### Ada Assessment by Study HCP (Stage 1)

After the recruitment process, the patients will consult with a study HCP, who is a mid-level HCP and will not be involved in the patient’s care. The study HCP will assess the patient using the prototype DDSS and create a differential diagnosis list. Depending on the patient allocation, there will be a difference in the synthesis of the final differential diagnosis list in the assessment (Figure 3): In arm 1, the study HCP will submit a preliminary list before seeing the prototype DDSS’s condition suggestion list. Once the preliminary list is submitted, the study HCP cannot change it. After being able to review the preliminary list and the prototype DDSS’s condition suggestion list, the study HCP will pick his or her top 5 differential diagnoses from both lists and submit a final differential diagnosis list. Conversely, in arm 2, the study HCP will see the prototype DDSS’s condition suggestion list before submitting a final differential diagnosis list. This will give the study HCP the opportunity to consider differential diagnoses from the prototype DDSS and add their own differential diagnoses to create a final differential diagnosis list. The degree to which these lists match the gold standard diagnoses will be judged in a later step by an unbiased physician panel, after the completion of patient recruitment and study data recording.

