**Figure 1 figure1:**
[figure not shown]
Screenshots showing the user interface of the tool in this study.

Dynamic questioning is delivered by the system’s underlying medical intelligence using a medical knowledge base built by medical doctors to define a Bayesian network. This Bayesian network allows approximate inference to be carried out. Based on a user’s answers, the system dynamically decides which questions to ask next in order to generate a list of potential conditions [24]. In this study, the Ada assessment was used to help mid-level HCPs gain relevant insights into the patient’s condition during their consultation by asking questions about the patient’s symptoms in an order determined by the system’s underlying reasoning engine. After the assessment, the HCP received a list of possible “condition suggestions” determined by the reasoning engine based on the patient’s presenting complaint and their symptoms. Along with these condition suggestions, the HCP was provided with additional information regarding the presentation of the disease, so that the HCP was able to make a more informed diagnosis.

The accuracy and comprehensiveness of the Ada platform has been validated in several studies of the Ada SAA [31-33]. In 2020, the Ada SAA, which uses the same medical reasoning as the prototype DDSS, was shown to be market leading in the accuracy of its condition suggestions and urgency advice compared to 7 other SAAs, and it had condition suggestions and safety performance comparable to United Kingdom general medical practitioners [31]. In a more recent study comparing 12 tools, the Ada SAA had the highest diagnostic accuracy at the first diagnosis (72%), while the next best SAAs achieved accuracies of 68% and 59.5%, respectively. Overall, the mean accuracy of all 12 SAAs was 37.7% [33]. When evaluating urgency advice, the Ada SAA was rated third best, with an accuracy of disposition of 64% (accuracy was 90% and 66.7%, respectively, for the first- and second-best SAAs), while the mean accuracy achieved by all SAAs was 57.7% [33].

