### Patient Presenting to the Clinic (Recruitment Process)

For the recruitment process, the study staff will work in close cooperation with the hospital staff in order to identify potentially eligible patients in the waiting room. Patients assessed as potentially eligible will be approached by the study staff. The study staff will provide them with detailed information about the study and obtain written informed consent if the patients decide to enroll in the study. In addition to their parent’s or caretaker’s consent, children aged between 9 and 18 years will be requested to sign an assent form themselves. Enrolled patients will receive a unique study ID that is not part of the usual health care record and will be allocated alternately to the 2 study arms.

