### Risk-Benefit Assessment

This study does not pose any risk to the patients, as it is solely observational; therefore, there is no need for additional safety management. Patients requiring immediate medical care and clinically unstable patients will be excluded. If patients are called into their appointment before the study HCP finishes the prototype DDSS assessment, they will be excluded from the study process and analysis and proceed to usual care, meaning there will be no delay in the diagnosis or treatment of any patient. Although there will be 2 extra consultations for patients enrolled in the study, these consultations will generally require less than 10 minutes; therefore, it is highly unlikely to delay a patient’s diagnosis or treatment.

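### Patients are allocated by alternation before an interview that is the same in both arms, so the study HCP may be able to guess the arm while questioning and entering data

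*Protocol article*

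**What the plan says.** In the recruitment section, patients receive a study ID on enrolment "and will be allocated alternately to the 2 study arms". The stage 1 section then starts the study HCP consultation once recruitment is complete, so the arm is fixed before the interview begins.

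The DDSS specifications section describes a single question flow and mentions no difference by arm. The text after Figure 1 says when the suggestions appear: "After the assessment, the HCP received a list of possible “condition suggestions” determined by the reasoning engine".

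The stage 1 section describes the arms as follows:

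- **General:** "Depending on the patient allocation, there will be a difference in the synthesis of the final differential diagnosis list in the assessment".
- **Arm 1:** "In arm 1, the study HCP will submit a preliminary list before seeing the prototype DDSS’s condition suggestion list". That list is then locked, and a final list is made from both.
- **Arm 2:** "Conversely, in arm 2, the study HCP will see the prototype DDSS’s condition suggestion list before submitting a final differential diagnosis list".

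The Risk-Benefit Assessment adds an exclusion that operates during stage 1: "If patients are called into their appointment before the study HCP finishes the prototype DDSS assessment, they will be excluded". It covers both the study process and the analysis. The eligibility section also excludes dropouts and protocol deviations from analysis.

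The second primary endpoint compares the accuracy and comprehensiveness of the study HCP's lists between the two arms. The first concerns the DDSS's own list.

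**The concern.** The study HCP runs the interview and enters the answers, and each answer determines the next question. An HCP who expects to commit to an own list first (arm 1) has a reason to question more carefully. One who expects to be shown suggestions (arm 2) has less reason. If the arm is known or guessed during the interview, the arms can differ before the step that distinguishes them. The second endpoint would then mix the order in which suggestions are seen with interview effort. The DDSS list behind the first endpoint is built from the same entries and could also vary by arm. The third endpoint is a within-arm comparison and carries no between-arm bias, although its preliminary list may reflect the same awareness.

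A lesser matter is that patients called away during the question flow are lost after allocation, although at that point nothing about their visit need depend on the arm.

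The article says the pilot is meant to try out methods and supply power calculations for a later randomized trial. A weakness in the allocation step would be carried into that trial.

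**Working it through.** The article derives no sample size, alpha or power, so there is no planned figure to reproduce. The check is of the order of events, followed by illustrations of scale.

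**Order of events**

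1. Enrolment, study ID and alternate allocation (recruitment section).
2. Question flow run by the study HCP, described identically for all patients (DDSS specifications).
3. Suggestions generated after the assessment (text after Figure 1).
4. List-making, where arm 1 and arm 2 differ (stage 1 section).

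Allocation stands at step 1, but it is first needed between steps 2 and 3.

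**Can the arm be guessed?** Whoever completes step 4 necessarily learns that patient's arm. If one HCP sees consecutive patients, strict alternation then gives away the next arm, whether or not the study ID reveals it. If several HCPs share the patients, one HCP's last patient no longer settles the next arm. The article does not give the number of study HCPs.

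**Sampling error.** Inputs: at least 50 patients (Study Optimization Phase), so about 25 per arm under alternation; accuracy p = 0.60 (assumed); loss rates (assumed). The 95% half-width of the arm difference is 1.96 × √(2 × p × (1 − p) / n).

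| Assumed loss | Analysed | n per arm | Half-width |
|---|---|---|---|
| 0% | 50 | 25 | 1.96 × √(0.48/25) = 0.272 |
| 10% | 45 | 22.5 | 0.286 |
| 20% | 40 | 20 | 0.304 |
| 30% | 35 | 17.5 | 0.325 |

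**Interview effort (all inputs assumed).** If knowing the arm changed the questioning in 20% to 40% of cases and moved accuracy by 10 to 20 points in those cases, the arm difference would shift by 0.2 × 10 = 2 to 0.4 × 20 = 8 points. Nothing in the article supports these inputs. They show only that even generous values stay well below 27 points.

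**Loss after allocation (all inputs assumed, no true arm effect).** Half the cases are easy (65% accuracy) and half hard (45%). Only hard cases are interrupted, at rate r. Accuracy among completers is f(r) = (0.5 × 0.65 + 0.5 × (1 − r) × 0.45) / (0.5 + 0.5 × (1 − r)).

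- f(0) = 0.550; f(0.1) = 0.5553; f(0.2) = 0.5611; f(0.4) = 0.575.
- Equal rates, 20% and 20%: spurious difference 0.
- 20% against 10%: 0.6 points.
- 40% against 20%: 1.4 points.
- 40% against 0%: 2.5 points.

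Loss biases the comparison only if it differs by arm, and even then the effect here is small.

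**The case against.** The strongest reply has five parts.

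- **Predictability comes from alternation, not from timing.** This stands. Moving alternate allocation to the end of the question flow would leave the next arm just as guessable, so a change of timing alone is not a remedy.
- **Knowledge of the arm is inferred.** This stands in part. A reader might conclude that the study HCP does know the arm, or that the article says the arms differ only after the question flow. It says neither. The second is the natural reading of two sections together, and Figure 3, which compares the arms, is not shown. When the HCP learns the arm may be set out in the full protocol. What remains is that nothing in the article conceals the arm, while the alternation it does state works against concealment.
- **The engine chooses the questions, so the HCP has little room to influence the DDSS list.** This weakens the route to the first endpoint, which is therefore only a possibility. The HCP still enters the answers and still forms the lists compared in the second endpoint.
- **Knowing that one must commit first may be part of the workflow being compared.** This is fair: the endpoint is not expressly limited to list order. But the article describes the arm difference as one of list synthesis, and an unmeasured difference in interviewing would make the result harder to interpret.
- **This is an unpowered pilot.** True, and it limits the importance of the point. It does not make an avoidable weakness worth keeping in a study meant to try out methods for a later trial.

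**Conclusion.** The point holds as a low-cost improvement in design, not as an error in any figure. Allocation by alternation precedes an interview described identically for both arms, and the article shows no concealment from the person who enters the data. The second primary endpoint is exposed; the first possibly so. The size cannot be derived from the document and is likely small beside a half-width of about 27 points (25 per arm, assumed accuracy 60%).

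Two stronger readings should be resisted. A reader might infer that excluding interrupted patients biases the arm comparison. Being called to an appointment is not described as depending on arm, and loss unrelated to arm costs precision only. A reader might also infer that later allocation would remove all such loss. It removes only losses during the question flow. Interruptions in arm 1's additional preliminary-list step would still fall after allocation, and that step is the more plausible source of unequal loss.

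**What to change.** 1. In the recruitment section, replace alternation with a randomly generated, concealed sequence. Because the HCP learns each arm in the end, the sequence must not be deducible from past patients; blocks of varying, undisclosed size would do this and keep the arms near equal.
2. In the stage 1 section, state that the arm is revealed, on the tablet or by sealed envelope, only after the last DDSS question is answered, and that a patient counts as allocated from that moment.
3. Compare the DDSS's own accuracy between arms as a check that the interviews were run alike. With about 25 per arm, this would detect only gross differences.
4. Report by arm every interruption after the reveal, including any during arm 1's preliminary-list step.

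**Cost.** A form setting or a set of envelopes, and amended wording in two sections. Whether the prototype can hold back the arm is not stated; envelopes avoid that question. Recruitment began in October 2021, so a change now puts two allocation procedures into the data. Report patients enrolled before and after the change separately. If that is not worthwhile so late, keep the present procedure, carry out the by-arm check and the by-arm report of interruptions, and adopt the new procedure for the later trial.

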**Figure 3 figure3:**
[figure not shown]
Comparison of study arms in stage 1. pDDSS: prototype diagnostic decision support system; DDL: differential diagnosis list.

Our limit of 5 differential diagnoses is a pragmatic limit based on Ada’s limit of 5 condition suggestions; it is similar to the approach taken in many other papers in the medical literature, which have used comparisons with a gold standard diagnosis and a maximum of 5 to 10 differential diagnoses [33-35]. The reasoning for this is that the length of a diagnostic list has been found to be a key predictor of accurate diagnosis retrieval; long diagnostic lists are less specific and hence problematic for clinicians using differential diagnosis tools in a busy clinical setting [10].

### Patient Examination by Usual HCP (Stage 2)

Having finished step 1, the patients will continue on to a consultation with a usual HCP. In this step, the patient’s diagnosis and a further diagnostic plan for them will be determined as a part of usual care. The usual HCPs will be COs, AMOs, or medical doctors. The usual HCPs in stage 2 will not be the same HCPs that performed the interview in stage 1. During the consultation, the usual HCPs will fill out a standardized electronic form and a structured consultation report form through a tablet-based electronic case report form (eCRF). Afterwards, they will complete the standard hospital forms, record vital signs, and request laboratory or diagnostic procedures as part of usual care.

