### Mid-level Health Care Workers

This study will be conducted in a district hospital in Tanzania, where the main entry point for patients into the health care system is primary care [15]. Primary care is delivered in an outpatient setting that includes dispensaries, health centers, and district hospitals [16]. In Tanzania, the health care staff shortage is severe; staffing is estimated to be 52% of the actual need [17]. Mid-level health care workers compensate for the insufficiency of qualified medical doctors by carrying out some aspects of the roles of doctors. Mid-level health care workers are a group predominantly found in LMICs [18]. They are defined as health care workers who undergo shorter training than physicians, but who nonetheless perform some roles generally considered part of a physician’s responsibilities [18]. In Tanzania, mid-level health care workers include clinical officers (COs) and assistant medical officers (AMOs) [19].

After graduating from secondary school, COs receive 3 years of practical and theoretical training. A CO’s responsibility is diagnosing and treating common conditions and performing minor surgeries. After gaining 3 years of practical experience, a CO can undergo a further 2 years of training to become an AMO. The position of an AMO involves a wider scope of medical practice; they can perform surgeries such as appendectomies and cesarean sections. Additionally, AMOs can act in leadership roles in medical facilities, especially in rural areas [19]. The prototype DDSS in our study will be used by COs. If there is no CO available for the patient consultation, then it will be used by an AMO. By evaluating the use of the prototype DDSS by mid-level HCPs, we aim to assess its potential to improve the performance of HCPs who have received less medical training than fully-qualified medical doctors.

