### Objective and Hypotheses

This study is part 2 of the AFYA (Artificial Intelligence-Based Assessment of Health Symptoms in Tanzania) study series [20]. The current study will explore the potential of the prototype DDSS to empower HCPs in LMICs. The objective is to measure to what degree the prototype DDSS can enhance the diagnostic accuracy of mid-level HCPs. This will be done by comparing, in an observational study setting, the diagnostic accuracy of HCPs who use the study tool to HCPs performing usual care, henceforth referred to as usual HCP, and by comparing the accuracy of diagnoses submitted before and after input from the DDSS. Since impracticality is a common barrier to CDSS adoption [8,9], we will also collect qualitative data on the usability, usefulness, and acceptance of the prototype DDSS. These measurements will provide insights on the appropriateness of the prototype DDSS interface.

There are two study hypotheses: (1) a “chatbot”-based DDSS, which is similar to a symptom assessment app (SAA) as it asks a series of questions about the patient’s symptoms using a sequential “question flow,” is an appropriate interface for improving the accuracy of decision-making by mid-level HCPs in sub-Saharan Africa; and (2) the diagnostic accuracy of mid-level HCPs will be improved by the use of a “question flow” DDSS based on a chatbot.

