### Data Analysis

Applying the definition from Gilbert et al [31], we will assess the accuracy and comprehensiveness of the top-1, top-3, and top-5 suggested conditions by the prototype DDSS in comparison to the gold standard differential diagnoses. Data analysis will also be carried out as presented by Gilbert. In short, descriptive tests and statistics appropriate for categorical data will be utilized to compare condition suggestion accuracy. To analyze if the proportion of correct condition suggestions from the prototype DDSS, from the usual HCPs, and from the study-provided physicians are drawn from the same distributions, the chi-squared test will be applied. If there is a significant difference, we will apply a 2-sided post hoc pairwise Fisher exact test to compare the prototype DDSS and the practitioners. Due to the low sample size of this pilot study, it may be the case that the chi-squared tests will not produce significant results. As the study goal is the comparison of the prototype DDSS to usual care, the ratings of the usual HCPs will be strictly anonymized.

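### Usual HCPs may include medical doctors while only COs or AMOs use the tool, so the tool-user versus usual-HCP contrast mixes tool effect with level of training

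*Protocol article*

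**What the plan says.** Objective and Hypotheses sets the target: "The objective is to measure to what degree the prototype DDSS can enhance the diagnostic accuracy of mid-level HCPs". It names two routes. The first compares "the diagnostic accuracy of HCPs who use the study tool to HCPs performing usual care, henceforth referred to as usual HCP". The second compares diagnoses given before and after the tool's input.

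The tool's users are all mid-level. Mid-level Health Care Workers says "The prototype DDSS in our study will be used by COs" and adds "If there is no CO available for the patient consultation, then it will be used by an AMO". Stage 1 agrees: "the patients will consult with a study HCP, who is a mid-level HCP and will not be involved in the patient’s care".

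The usual-care side is wider. Stage 2 says "The usual HCPs will be COs, AMOs, or medical doctors", and also "The usual HCPs in stage 2 will not be the same HCPs that performed the interview in stage 1". No proportions are given.

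Data Analysis takes usual HCPs as a single group, next to the tool and the study-provided physicians, in a chi-squared test followed by pairwise Fisher tests. It describes the study goal as the tool against usual care and says that "the ratings of the usual HCPs will be strictly anonymized". The article states no restriction, stratification or adjustment by cadre. Its limitations section does not mention the mixed comparator.

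**The concern.** In the first route, two things differ between the sides: whether the tool was used, and what training the practitioner may have had. The objective concerns only the first. A difference between the sides, or the lack of one, could partly reflect how many doctors were on duty in the outpatient clinic.

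The article itself treats training as relevant. It justifies the study by the shorter training of COs and AMOs, and it cites a review suggesting that less experienced users are more likely to benefit from such systems.

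The pilot is also meant to support power calculations for a later randomized trial. An estimate of mid-level gain taken from this contrast would carry the doctor mix into that calculation. More patients would not remove the bias, and if cadre is not kept in the data, no later analysis could remove it either.

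**Working it through.** There is no planned figure to reproduce. The minimum of 50 participants is declared pragmatic, and no alpha, power or effect size is given. The check is a comparison of the two sides, then a scale calculation on assumed values.

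**Step 1: the two sides of the contrast**

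| | Tool users (stage 1) | Usual HCPs (stage 2) |
|---|---|---|
| CO | yes, by default | yes |
| AMO | yes, if no CO is available | yes |
| Medical doctor | no | yes |
| Same individuals on both sides | no | no |

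The sides differ in permitted cadre, and nothing in the article separates that from tool use.

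**Step 2: direction and formula.** Let *p* be the accuracy of unaided mid-level staff, *g* the true gain from the tool, *f* the share of patients whose usual HCP is a doctor, and *d* the doctor-minus-mid-level accuracy gap on those patients.

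- Tool users: p + g
- Usual HCPs: (1 - f)p + f(p + d) = p + fd
- Observed difference: g - fd, so the bias is -fd

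The bias is zero if no usual HCP is a doctor, and it runs against the tool if d is positive.

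**Step 3: size.** The documents give neither *f* nor *d*, so both are assumptions. The entries are f × d, in percentage points.

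| Doctor share | d = 10 | d = 20 |
|---|---|---|
| 20% | 2 | 4 |
| 40% | 4 | 8 |
| 60% | 6 | 12 |

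For an assumed true gain of 10 points and 50% doctors, the observed difference would be 10 - 0.5 × 10 = 5 points at a gap of 10, and 10 - 0.5 × 20 = 0 at a gap of 20. With a gap of 5 it would be 7.5.

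**Step 4: scale.** The only benefit the article quotes in an LMIC setting is 82.4% against 74.1%, or 8.3 points, from family medicine residents in Mexico. Only the 60% share with a 20-point gap exceeds it; the 40% share with a 20-point gap comes close.

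For random error, take 50 patients on each side, accuracy near 60% and independent groups (all assumed). The 95% half-width is 1.96 × √(2 × 0.6 × 0.4 / 50) = 0.192, about 19 points. This is only a rough guide, since the same patients appear on both sides.

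**The case against.** The strongest reply has four parts.

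- **Other endpoints.** The second primary endpoint (arm 1 against arm 2) and the third (preliminary against final list in arm 1) use only mid-level study HCPs. The third also compares lists from the same practitioner for the same patient. This stands: neither has the training mismatch. One limit is that stage 1 places the preliminary list before sight of the condition suggestions, not before use of the tool. As the text reads (Figure 3 is not shown), that list may already reflect the question flow. The usual HCPs would then be the only comparator containing mid-level staff with no exposure to the tool.
- **Usual care as delivered.** The first primary endpoint and the tests in Data Analysis score the tool's own list, not the list of a practitioner using it. If doctors are part of usual care at this hospital, the pooled group is a legitimate comparator for that question. This also stands.
- **Anonymization.** A reader might infer that strict anonymization deletes cadre. The article does not say so. Cadre is a non-identifying category that anonymized data can carry; the article simply does not say that it is kept. Loss of the link to individual practitioners is the more plausible effect.
- **Proportion.** The study is a pilot declared not powered for its hypotheses. The illustrative 19-point half-width exceeds every bias in the table, and all the shares and gaps are assumed. This limits the urgency. It does not answer the point, because the mismatch is fixed by design and does not shrink with more patients.

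**Conclusion.** The point holds for one contrast: practitioners using the tool against usual practitioners, when it is read as the gain for mid-level staff. As written, that contrast cannot separate the tool's effect from level of training. If doctors are more accurate, a favourable result would be conservative and still informative, while a null or unfavourable one would be ambiguous.

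The size cannot be known from the documents. The 2-12 points rest entirely on assumed doctor shares of 20-60% and gaps of 10-20 points.

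A reader might go further and conclude that the comparison with usual care says nothing about mid-level staff, or that the study cannot meet its objective. The documents do not support that. Usual HCPs include COs and AMOs, so part of the contrast is already mid-level against mid-level. The before-and-after route does not have this mismatch. The matter is worth correcting because the correction is cheap, not because the design fails without it.

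**What to change.** 1. Keep two coded items for each stage 2 consultation in the analysis file: cadre (CO, AMO, doctor) and a practitioner ID that identifies nobody.
2. Reword the anonymization sentence in Data Analysis so that it clearly allows both codes.
3. Keep the pooled usual-HCP figure as the comparator for usual care as delivered.
4. Report usual-HCP accuracy by cadre. For any statement about gain in mid-level HCPs from this contrast, use the patients whose usual HCP was a CO or AMO, with the study HCP's lists taken from those same patients.

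The cost is two coded fields, some wording, and less precision in the stratum. By the formula above, with 50 patients in all and doctor shares of 20%, 40% or 60%, the stratum has 40, 30 or 20 patients. The half-width is then 1.96 × √(0.48/40) = 21, 1.96 × √(0.48/30) = 25 or 1.96 × √(0.48/20) = 30 points, against 19 for the pooled group. The stratum result should therefore be presented as descriptive.
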